## 6. PROJECT DESIGN

### 6.1 Type of research and general project design

#### 6.1.1 Type of research

Research project in which biological material is sampled and/or health-related personal data is collected and will be used for further research including the development of an algorithm for VIA classification. Coded data will be used.

#### 6.1.2 Study design

Single-center prospective and longitudinal (cohort) study

### Procedures

The management will be as follows:

#### First visit

- Information about the study and written informed consent
- Information about cervical cancer, STDs (including HIV) and fistula will be given to women;
- Socio-demographic data, acceptability of the self-test and data on women's quality of life will be collected according to validated questionnaire;
- HPV tests will be carried out on self-collected vaginal (flocked swabs transported in a 0.9% sodium chloride) medium samples using the GeneXpert machine. The results will be available after one hour.
- HPV-negative women will be reassured and advised to do the next screening 5 years later.
- HPV-positive women will undergo the following sequence on the same day: VIA/VILI > Pap smear

- > Cervical Biopsy (VIA-guided biopsy for VIA-positive participants and random biopsy for VIA-negative participants) > Endocervical Curettage (ECC). These tests will be done by the following experienced physicians.
- Pictures of the cervix during VIA/VILI (native image, video during acetic acid and image after lugol's iodine) will be stored on a digital device.
- VIA/VILI will be interpreted on smartphone pictures according to the ABCD criteria (relaxed IARC criteria).
- All participants with a positive VIA/VILI will be treated with thermal ablation if eligible or Loop Electrosurgical Excision Procedure (LEEP for participants ineligible to thermal ablation).
- Specimens of Pap smear will be transported in BD SurePath™ vials (Becton Dickinson Company, Franklin Lakes New Jersey, USA) while those of biopsy, LEEP and ECC will be transported separately in formol (formaldehyde solution) vials.
- Cytological and histological analyzes will be conducted both in Yaoundé and in Geneva.

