### **4.3 Risk-Benefit Assessment**

The study participants will benefit from a free screening for cervical cancer with HPV test. HPV- positive women will undergo, Pap smear, ECC, VIA/VILI and biopsy. Those with positive VIA will immediately be treated by thermal ablation or LEEP (if not eligible to thermal ablation). All cancer and pre-cancer detected will have free of charge management.

Voluntary women will be addressed to the HIV department for screening and free treatment. Patients with fistulas will be transferred to the University Teaching Hospital of Yaoundé and will be freely treated (collaboration between Pr [name] and the Swiss NGO “fistula- group” lead by [name], Geneva).

We expect that our data will determine how a CC-screening program might be established in a sustainable prevention strategy. The data will also determine the level of support, which will be needed to maintain high-quality CC prevention services in equipment and provider skills. In addition, the developed AVC tool will assist medical staff in their assessment of VIA and reduce the subjectivity of the process.

One possible risk is the unauthorized data access or unwanted identification of project participants. Another risk though very low is the occurrence of side effects following biopsy and thermal coagulation (light pelvic pain, light vaginal bleeding or watery discharge).

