## **5. OBJECTIVES, ENDPOINTS/ OUTCOMES AND OTHER STUDY VARIABLES**

### **5.1 Objectives**

#### **5.1.1 Main objective**

- To determine the sensitivity and specificity of VIA/VILI to detect CIN2+ among HPV-positive women, using histology as gold standard

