#### **6.1.5 Sample collection:**

Vaginal specimens for HPV test will be collected by participants themselves using flocked swabs after explanations by co-investigators. Two transport mediums will be used for those self-collected vaginal samples: NaCl 0.9%.

Cervical images will be obtained using a Smartphone (Samsung). The first image is that of the native cervix. The second part involves a 2-minute video of 1 frame/second (120 images) captured during application of a 5% acetic acid solution.-The third image is taken following application of Lugol's iodine.

Cervical biopsy will be guided by VIA/VILI if positive. It will be done at 6 o'clock in the transformation zone for participants with negative VIA/VILI. Biopsies will be performed by trained staff using Tischler forceps (Farla medical, United Kingdom).

Pap smear samples will be obtained with a spatula and transported in BD Surepath® vials (Becton Dickinson Company, Franklin Lakes New Jersey, USA) or ThinPrep (Hologic, Bedford, MA, USA). ECC will be done with an endobrush.

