## 8. PROJECT ASSESSMENTS

### 8.1 Project flow chart/ table of procedures and assessments

[figure not shown]

Figure 1. Flow chart of the study

Use of GeneXpert® test; If suspicious of cancer refer to tertiary center;  All HPV positive women will have as quality control a cytology and guided biopsy (or random biopsy if VIA/VILI normal); a recall will be done if abnormal cytology/histology in untreated women. LEEP (Loop electrosurgical Excisional Procedure) in case of ineligibility to Thermal ablation. HPV: Human papillomavirus; LEEP: Loop electrosurgical excision procedure; VIA: Visual inspection with acetic acid; VILI: Visual inspection with Lugol's iodine

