### **8.5.2 Assessment and Documentation of SEs**

Application and interpretation of the VIA results will be conducted as recommended by the WHO. « Relaxed » VIA criteria will be used, meaning that any whitening of the cervix after acetic acid application will be considered as positive (to reduce false negative rate). Application of acetic acid on the cervix may cause a slight burning sensation, which disappears after a few minutes. The application of iodine does not cause any discomfort if not a change in color of the cervical surface, but the normal color returns a few minutes after the procedure. As for the cell and tissue specimens, minor pain and/or bleeding may be observed after sampling. But most often, these inconveniences are harmless and disappear within hours after the procedure. All the SEs will be documented in the participants' file and on the SE report form.

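### Two rules for the reference-standard biopsy (by VIA alone, or by VIA/VILI) and no rule for combining the two readings, so tissue from VIA-negative, VILI-positive women is not fixed

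*Protocol*

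**What the plan says.** The main objective (protocol, 5.1.1) is "To determine the sensitivity and specificity of VIA/VILI to detect CIN2+ among HPV-positive women, using histology as gold standard". The index test is therefore VIA/VILI, and the biopsy is central to the reference standard.

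On where the biopsy is taken:
- **First visit (under 6.1.2), and the English and French synopses:** "VIA-guided biopsy for VIA-positive participants and random biopsy for VIA-negative participants".
- **6.1.5:** "Cervical biopsy will be guided by VIA/VILI if positive", and otherwise at 6 o'clock "in the transformation zone for participants with negative VIA/VILI".
- **Flow-chart footnote (sections 1 and 8.1):** "guided biopsy (or random biopsy if VIA/VILI normal".

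On who is treated the same day:
- **First visit and synopsis:** "All participants with a positive VIA/VILI will be treated with thermal ablation if eligible", with LEEP for the ineligible.
- **4.3:** "Those with positive VIA will immediately be treated by thermal ablation or LEEP".

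On what counts as positive, the first-visit text names the ABCD criteria, and the abbreviation list expands the letters. The only explicit rule is in 8.5.2: "any whitening of the cervix after acetic acid application will be considered as positive". No section says how a VIA result and a VILI result are merged.

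**The concern.** The rules give different instructions for a woman who is negative on acetic acid but positive on Lugol's iodine. The first-visit text gives her a random biopsy. Section 6.1.5 and the footnotes give her a guided one if VILI alone makes VIA/VILI positive. On that same reading the first-visit text also has her treated that day, before histology is known.

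If she has a CIN2+ lesion that the non-guided biopsy and the curettage both miss, and thermal ablation follows, she sits in the positive row of the 2x2 table but is recorded as disease-free. A true positive has become a false positive. The error runs in one direction, so recruiting more women would not remove it. It arises when tissue is taken, so it cannot be repaired at the analysis stage.

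**Working it through.** **Step 1. The sections side by side, for a VIA-negative, VILI-positive woman.**

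| Section | Biopsy | Same-day treatment |
|---|---|---|
| First visit; synopsis | random | yes, if VILI alone makes VIA/VILI positive |
| 6.1.5; flow-chart footnote | guided, if VILI alone makes VIA/VILI positive | – |
| 4.3 | – | no, if VIA is read literally |
| 8.5.2 | – | not stated; positivity is defined by whitening only |

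A further mismatch concerns negatives: the biopsy called random in the first-visit text is at a fixed 6 o'clock site in 6.1.5.

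**Step 2. The plan's own figures (9.1).** HPV-positive: 6000 × 0.20 = 1200. CIN2+: 1200 × 0.10 = 120, and 120 × 0.8 = 96 analysed. Non-CIN2+: 1080 × 0.8 = 864. Half-widths, 1.96 × √(p(1−p)/n):
- sensitivity: 1.96 × √(0.6 × 0.4/96) = 0.098, stated as 9.8%
- specificity: 1.96 × √(0.5 × 0.5/864) = 0.033, stated as 3.3%

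Both reproduce.

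**Step 3. Expected table without the problem.** True positives 0.6 × 96 = 57.6; false negatives 38.4; false positives 0.5 × 864 = 432; true negatives 432. Index positives: 57.6 + 432 = 489.6. PPV = 57.6/489.6 = 11.8%.

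**Step 4. Effect of missed lesions.** Two inputs are not in the documents and are assumed:
- f, the share of all analysed CIN2+ that is VIA-negative, VILI-positive: 2% to 12%. The upper value is one fifth of the true positives: 0.2 × 57.6 = 11.52, and 11.52/96 = 12%.
- m, the fraction of those lesions missed by non-guided biopsy plus curettage: 25% to 75%.

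The calculation takes 60% and 50% as values for the combined test, counts VILI-only as positive, has every such woman biopsied under the first-visit text, and lets no LEEP specimen recover a case. Then lost = 96 × f × m, and
- sensitivity = (57.6 − lost)/(96 − lost)
- specificity = 432/(864 + lost)
- PPV = (57.6 − lost)/489.6

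| f | m | lost | sensitivity | specificity | PPV |
|---|---|---|---|---|---|
| 2% | 25% | 0.48 | 57.12/95.52 = 59.8% | 432/864.48 = 50.0% | 11.7% |
| 5% | 50% | 2.40 | 55.20/93.60 = 59.0% | 432/866.40 = 49.9% | 11.3% |
| 10% | 75% | 7.20 | 50.40/88.80 = 56.8% | 432/871.20 = 49.6% | 10.3% |
| 12% | 75% | 8.64 | 48.96/87.36 = 56.0% | 432/872.64 = 49.5% | 10.0% |

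Sensitivity falls by 0.2 to 4.0 points, and specificity by at most 0.5.

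**Step 5. Would excluding these women help?** Remove a share s of the index positives, diseased or not, and no negatives. Sensitivity = 57.6(1−s)/(96 − 57.6s); specificity = 432/(432 + 432(1−s)).
- s = 5%: 54.72/93.12 = 58.8%; 432/842.4 = 51.3%
- s = 10%: 51.84/90.24 = 57.4%; 432/820.8 = 52.6%
- s = 20%: 46.08/84.48 = 54.5%; 432/777.6 = 55.6%

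For sensitivity, exclusion is equivalent to assuming that every such lesion is missed (m = 100%). It also inflates specificity.

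**The case against.** The strongest reply is that VIA is often shorthand here for the combined test. Section 9.1 sizes the study on VIA while the endpoint is VIA/VILI, and the French synopsis analyses VIA alone where the English has VIA/VILI. Both inspections precede the biopsy, so the operator already has the Lugol result. This makes the practical conflict smaller, but the text does not say that the terms are interchangeable, and the synopsis once separates them by comparing the VIA/VILI reading with VIA. The shorthand reading is also what Step 4 needs: if the 60% in 9.1 is for acetic acid alone, the VILI-only cases lie outside the 57.6 and the arithmetic is only indicative.

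Second, the premise that VILI alone makes a woman positive is not established. Read literally, 4.3 and 8.5.2 leave her index-negative and untreated that day. A missed lesion would then turn a false negative into a true negative, so even the direction of the bias depends on the missing definition. This stands, and it is why the point is conditional.

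Third, a reader might infer that the lesion's histology is always lost, or that the trial would wrongly find that Lugol's iodine adds nothing. The documents support neither. Curettage is also taken and counts as histology (6.1.4), a random biopsy may hit the lesion, and a LEEP specimen is kept for analysis. No listed objective or endpoint tests the added value of Lugol.

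**Conclusion.** The contradiction is real and lies in current operative text. The sections disagree on what decides the biopsy site and on what triggers same-day treatment, and none defines a positive combined result. The reference tissue for the primary endpoint is therefore not fixed for VIA-negative, VILI-positive women.

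The harm is conditional. It needs VILI-only positivity to count as positive, the first-visit biopsy rule to be followed literally, and thermal ablation to follow without the lesion having been sampled. The true size is unknown. Under the assumed ranges the loss of sensitivity is about 0.2 to 4 points, within the planned half-width of 9.8 but systematic; PPV falls from 11.8% to between 11.7% and 10.0%, and the effect on specificity is negligible. This is a modest point that deserves correction because it concerns the reference standard and costs little to settle.

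**What to change.** - Reconcile the English and French synopses, 4.3, the first-visit procedure in 6.1.2, 6.1.5, the flow-chart footnotes in sections 1 and 8.1, and 8.5.2. One stated definition of a positive test should be used consistently for the biopsy site, the treatment trigger and the row of the 2x2 table. Which rule that is belongs to the investigators.
- Record on the CRF the VIA result, the VILI result, and whether the biopsy was guided or taken at 6 o'clock.
- For women already enrolled, report how many VIA/VILI-positive women had a non-guided biopsy. Show bounds for sensitivity and specificity over a stated range of miss rates, next to the primary analysis.
- Do not exclude these women: removing index positives only biases both measures (Step 5).

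The cost is wording changes, a few CRF fields and one supplementary table. Every HPV-positive woman already has a biopsy, so no procedure is added. For past visits, the biopsy type may have to be recovered from existing records.

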#### **Visit to inform results**

- Results of cytological and histological analyses will be explained to participants by a gynecologist-obstetrician (co-investigator). Participant who tested positive for HPV but have normal results for the other exams (VIA/VILI, Pap smear, Cervical biopsy and ECC) will be given an appointment for follow-up at 12 months. Participants with abnormal results will receive comprehensive treatment (thermal ablation or LEEP for CIN2+ and appropriate management for invasive cancers).

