| Measurements and Procedures: | 
Primary (Flow chart)
 
 
- After a community-based sensitization campaign, participants will undergo HPV-testing with GeneXpert® machines using self-collected samples (Flocked swabs) transported in a 0.9% sodium chloride (NaCl 0.9%) medium,
 
- HPV-negative women will be reassured and advised to do the next screening 5 years later,
 
- HPV-positive women will undergo the following sequence on the same day: VIA/VILI > Pap smear > Cervical Biopsy (VIA-guided biopsy for VIA-positive participants and random biopsy for VIA-negative participants) > Endocervical Curettage (ECC). All participants with a positive VIA/VILI will be treated with thermal ablation if eligible or Loop Electrosurgical Excision Procedure ((LEEP) for participants ineligible for thermal ablation).
 
- Specimens of Pap smear will be transported in BD SurePath™ vials (Becton Dickinson Company, Franklin Lakes New Jersey, USA) or ThinPrep™ (Hologic, Bedford, MA, USA) while those of biopsy, LEEP and ECC will be transported separately in formol (formaldehyde solution) vials.
 
- VIA/VILI will be interpreted on Smartphone images according to ABCD criteria and compared to VIA.
 
- Results of cytological and histological analysis will be disclosed to participants by midwives or obstetrician-gynecologist. Those requiring additional treatment will receive it for free.
 
- Follow-up visits will be organized 6 and 12 months later for women having received a treatment (self HPV GeneXpert® test > VIA/VILI > Pap smear > Guided biopsy + ECC).
 
 
Follow-up visits will be organized 12 months later for women having a positive screening test but VIA/VILI negative (self HPV GeneXpert® test > VIA/VILI > Pap smear > Guided biopsy + ECC)
 
Secondary
 
 
- Pictures of the cervix (native, after application of acetic acid (VIA) and lugol's iodine (VILI)) will be taken using a Smartphone (Samsung Galaxy™ S5). In addition to these 3 pictures, a 120 second long video of the cervix (120 images) will be recorded during the VIA. Then a database will be built-up.
 
- During the visit, participants will receive information on gynecological pathologies, including cervical cancer, sexually transmitted diseases and HIV, vaginal fistula
 
- All participants diagnosed with pre-cancer or cancer of the cervix will receive free of charge treatment
 
- Participants treated by thermal ablation and an equivalent number of untreated patients (about 250 in each group) will be followed up by phone or interview for a survey on fertility and obstetrical
 
 |

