| Mesures et Procédures:              | 
Objectif primaire (Flow chart)
 
 
- Après une campagne de sensibilisation communautaire, les participantes feront un auto-prélèvement vaginal avec des bâtonnets floqués transportés dans un milieu de Chlorure de Sodium à 0,9% en vue d'un test HPV rapide (GeneXpert®).
 
- Les participantes HPV-négatives seront rassurées et conseillées en vue d'un prochain test HPV cinq ans plus tard.
 
- Les participantes HPV-positives suivront la séquence ci-après le même jour: IVA/IVL > Frottis cervical > Biopsie cervicale (guidée par l'IVA pour les participantes IVA-positives et aléatoire pour les patientes IVA-négatives) > Curetage endocervical (CEC). Toutes les participantes IVA/IVL-positives seront traitées par thermal coagulation ou par conisation à l'anse diathermique selon l'éligibilité.
 
- L'IVA/IVL seront interprétés sur la base de photographies smartphones selon les critères ABCD
 
- Les spécimens de frottis cervical seront transportés dans des flacons BD SurePath™ (Becton Dickinson Company, Franklin Lakes New Jersey, USA) ou ThinPrep™ (Hologic, Bedford, MA, USA) et ceux des biopsies, de CEC et de conisation seront transportés séparément dans du formol.
 
- Les résultats des analyses cytologiques et histologiques seront expliqués aux participantes par une sage-femme ou un gynécologue-obstétricien-ne. Celles ayant des indications à un traitement supplémentaire le recevront gratuitement.
 
- Des visites de suivi seront organisées à 6 et 12 mois pour les femmes qui ont été traitées (HPV GeneXpert® test par autoprélèvement > IVA/IVL > frottis cervical > biopsie guidée + CEC).
 
 
Objectifs secondaires
 
 
- Des photographies du col (natif et après application d'acide acétique et du lugol) seront réalisées avec un smartphone (Samsung Galaxy™ S5). En plus des 3 photographies, une vidéo de 2 minutes (120 images) sera prise lors de l'IVA. Elles seront utilisées pour constituer une base de données.
 
- Au cours de la première visite, les participantes recevront des informations sur les pathologies gynécologiques (cancer du col de l'utérus, fistules obstétricales et maladies sexuellement transmissibles).
 
- Tous les cancers et pré-cancers du col utérin dépistés seront traités gratuitement.
 
 |

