### 5.2.2 Secondary endpoint/outcomes

- Provide teaching material for professional training on cervical cancer prevention through VIA/VILI (cervical images database)
- Sexual dysfunction score, score of anxiety and method of contraception after screening procedures
- Willingness to participate in the 3T screening program;
- Prevalence of HPV, cervical pre-cancer and cancer among Cameroonian women
- HPV clearance at 6 and 12 months follow up
- Prevalence of CIN2+ disease at the 12-month follow-up
- Acceptability of self-HPV test, thermal ablation and cervical cancer screening procedures
- Women's experiences and attitudes on cervical cancer screening
- Proportion of side effects and complications after thermal ablation or LEEP
- VIA test-positive rate (HPV-positive women);
- VIA test-positive rate after 1- year follow-up of VIA-negative tests
- Thermal ablation efficacy
- Increase awareness on gynecological pathologies, including cervical cancer, sexually transmitted diseases and HIV, vaginal fistula in the community of the study area
- Number of women screened with and without the participation of community health care workers.
- Specificity and sensitivity of the AVC test, using histology as the reference standard
- Acceptability of the AVC test

The demand for programs to control CC in low-resource settings is strong. Lessons that we have learned from our previous experience, combined with results of recent researches have put our group in an excellent position to identify innovative and cost-effective strategies for reducing CC morbidity and mortality in developing countries. The obtained data will determine the level of support, which will be needed to maintain high-quality CC prevention services in equipment and provider skills. We expect also that our data will also determine how a CC- screening program might be established in a sustainable prevention strategy.

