## **9. STATISTICAL METHODOLOGY**

### **9.1 Determination of Sample Size**

We plan to include 6000 women in the study. Assuming a prevalence of HPV infection of 20%, 1200 participants will be HPV+. Among the awaited 1200 HPV+ women, 120 will have CIN2+ lesions (assuming a prevalence of CIN2+ of 10% among HPV+ women). Assuming a 20% drop-out rate, 96 cases of CIN2+ will be analyzed to determine the sensitivity of VIA (expected around 60%) with a precision of +/- 9.8%.

Among the awaited 1200 HPV+ women, 1080 will not have CIN2+ lesions. With a drop-out rate of 20%, 864 cases of non-CIN2+ will be analyzed to determine the specificity of VIA (expected around 50%) with a precision of +/- 3.3%.

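### The English synopsis and section 6.1.2 set different entry rules for the 12-month visit of HPV-positive, VIA/VILI-negative women, so the 1-year VIA outcome could rest on a selected subset

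*Protocol*

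**What the plan says.** Four parts of the protocol bear on who is seen at 12 months without having been treated at the first visit.

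- **English synopsis, Measurements and Procedures:** "Follow-up visits will be organized 12 months later for women having a positive screening test but VIA/VILI negative". The only conditions are the HPV result and the VIA/VILI result.
- **Section 6.1.2, Visit to inform results:** the 12-month appointment is for "Participant who tested positive for HPV but have normal results for the other exams (VIA/VILI, Pap smear, Cervical biopsy and ECC"). The next sentence sends women with abnormal results to treatment, but spells that treatment out only for CIN2+ and for invasive cancer.
- **French synopsis, Mesures et Procédures:** "Des visites de suivi seront organisées à 6 et 12 mois pour les femmes qui ont été traitées". The sentence on VIA-negative women in the English synopsis has no counterpart here. The French outcome list nevertheless includes 1-year VIA positivity in VIA-negative women.
- **Flow-chart footnote 3 (sections 1 and 8.1):** untreated women with abnormal cytology or histology are recalled. No visit date is attached.

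The post-treatment paragraph of section 6.1.2 gives treated women visits at 6 and 12 months. Section 6.1.6 says which tests are done at follow-up, not who attends.

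The outcome that depends on these rules is in section 5.2.2: "VIA test-positive rate after 1- year follow-up of VIA-negative tests". Its population is defined by the VIA result alone.

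**The concern.** The two rules select different women. Take an HPV-positive, VIA-negative woman whose biopsy shows CIN1, or whose only abnormality is the smear. The English synopsis gives her a 12-month visit. Under section 6.1.2 she is not normal on every test, so that appointment is not hers; nor does she have CIN2+ or cancer, so no treatment is specified that would place her in the 6- and 12-month post-treatment visits. She may be recalled, but the text does not say what follows the recall.

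The outcome in section 5.2.2 fits the synopsis rule. Staff working from section 6.1.2 would produce a denominator filtered on baseline cytology and histology. Women with a baseline abnormality plausibly have a higher chance of a positive VIA a year later, so the reported rate would probably be too favourable. An analysis plan can define a denominator, but it cannot recover visits that were never scheduled.

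**Working it through.** **1. The plan's own figures (section 9.1).** The inputs are "We plan to include 6000 women in the study", "Assuming a prevalence of HPV infection of 20%, 1200 participants will be HPV"-positive, "assuming a prevalence of CIN2+ of 10% among HPV+ women", and 20% drop-out.

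- HPV-positive: 6000 × 0.20 = 1200. With CIN2+: 1200 × 0.10 = 120. Without: 1080.
- After drop-out: 120 × 0.8 = 96 and 1080 × 0.8 = 864.
- Half-width of the 95% interval, 1.96 × √(p(1−p)/n): 1.96 × √(0.6 × 0.4/96) = 9.8% for sensitivity; 1.96 × √(0.5 × 0.5/864) = 3.3% for specificity.

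Both agree with the protocol (for sensitivity: "96 cases of CIN2+ will be analyzed to determine the sensitivity of VIA (expected around 60%) with a precision of +/- 9.8"%). It gives no sample size for the follow-up of VIA-negative women.

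**2. Expected VIA-negative group, same inputs (60% sensitivity, 50% specificity).**

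- With CIN2+: 120 × (1 − 0.60) = 48.
- Without CIN2+: 1080 × 0.50 = 540.
- Total: 588, of whom 48/588 = 8.2% have CIN2+. After 20% drop-out, about 470.

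Section 4.1 cites VIA sensitivities from 25% to 80%. At 25% the group is 90 + 540 = 630 (14.3% with CIN2+); at 80% it is 24 + 540 = 564 (4.3%).

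**3. Women covered by each rule.** The synopsis rule covers all 588. The section 6.1.2 rule covers at most the 540 without CIN2+, less those with CIN1 or an abnormal smear or ECC. That share, s, is not in the protocol; the values below are assumptions. Covered = 540 × (1 − s); left between the rules = 540 × s.

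| s (assumed) | Covered by 6.1.2 | Share of 588 | Between the rules |
|---|---|---|---|
| 0% | 540 | 92% | 0 |
| 10% | 486 | 83% | 54 |
| 20% | 432 | 73% | 108 |
| 30% | 378 | 64% | 162 |
| 40% | 324 | 55% | 216 |

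**4. Effect on the rate.** Let r_n and r_a be the 1-year VIA-positivity rates in women normal and abnormal at baseline. Among the 540, the full-group rate is (1 − s)·r_n + s·r_a. The section 6.1.2 rule reports r_n. The shortfall is s × (r_a − r_n): 0.1 to 0.4 times the difference in rates for the assumed range. The protocol gives neither r_n nor r_a, so no value in percentage points can be stated.

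**5. The 48 women with CIN2+.** Section 6.1.2 provides treatment for them, and treated women are seen at 6 and 12 months. They are not lost, but their 12-month result follows treatment. Section 5.2.2 does not say whether it counts.

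**The case against.** The strongest reply is that section 6.1.2 does not say that only women with all tests normal are seen at 12 months. It can be read as a complete two-way split: normal results lead to the 12-month appointment, abnormal results to treatment and then to the 6- and 12-month visits. The flow-chart footnote adds a recall for untreated women with abnormal findings. On this reading nobody is dropped.

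Part of this stands. It is not established that these women are lost to follow-up, and the recall shows an intention not to abandon them. But the split closes the gap only if every abnormality, including CIN1 and an isolated abnormal smear, leads to treatment; the text specifies treatment for CIN2+ and cancer only, and the recall has no date. Even on that reading, these women leave the untreated group, and their 12-month VIA result is a post-treatment result. Either way, the untreated women seen at 12 months under section 6.1.2 are those with every baseline test normal.

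A reader might also infer from the French synopsis that untreated women are not followed at all. The documents do not support that: the sentence is merely absent, and the French outcome list presupposes the visit.

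**Conclusion.** The point holds as an inconsistency in the follow-up rules with a consequence for one stated secondary outcome. The English synopsis and section 6.1.2 define different 12-month groups, and only the synopsis rule matches the outcome in section 5.2.2.

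The selected denominator arises only if section 6.1.2 is the rule that sites apply; under the synopsis rule the whole VIA-negative group of about 588 is followed. The figure of 54 to 216 women between the rules rests on an assumed 10% to 40% share. That the omitted women are at higher risk is plausible but not shown in the protocol.

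Two stronger conclusions are not supported. A reader might infer that 12-month HPV clearance and CIN2+ prevalence are biased in the same way; section 5.2.2 names no untreated population for either, so this cannot be concluded. A reader might also infer that the accuracy results are compromised. They are not: every HPV-positive woman is to have biopsy and ECC at the first visit, so baseline sensitivity, specificity and their precision are untouched.

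**What to change.** Reconcile the English synopsis, the French synopsis, the results-visit and post-treatment paragraphs of section 6.1.2, and flow-chart footnote 3 (both places), so that every HPV-positive, VIA/VILI-negative woman has one stated follow-up path, whatever her cytology and histology show. Which clinical follow-up rule is right is for the investigators and is not judged here.

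In section 5.2.2, state the denominator of the 1-year VIA outcome as all women VIA/VILI-negative at baseline. Say how women treated after recall are counted, so that they are not dropped silently. Report the result separately for women with normal and with abnormal baseline cytology or histology.

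The cost is wording, plus at most the visits the English synopsis already promises. The 12-month figures may turn out less favourable.
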